## Abstract

**Background:**

Quadriceps training is necessary in function and activity of daily living for patients with knee osteoarthritis (KOA). However, it did not reduce the rate of surgical treatment for end-stage KOA in the long term. This may be related to brain structure changes and maladaptive plasticity in KOA patients. Transcranial Magnetic Stimulation (TMS) could enhance the functional connectivity of brain regions and improves maladaptive plasticity. However, the synergistic effect of the combination of the two for treat KOA is still unclear. Therefore, the purpose of this study is to investigate whether the High-Frequency rTMS combined with quadriceps strength training can improve the pain and function in KOA more effectively than quadriceps training alone and explore the mechanism of action.

**Methods:**

This study is an assessor-blind, sham-controlled, randomized controlled trial involving 12 weeks of intervention and 6 months follow-up. 148 participants with KOA will receive usual care management and be randomized into four subgroups equally, including quadriceps strength training, high-frequency rTMS training, sham rTMS and quadriceps strength training, high-frequency rTMS and quadriceps strength training. The rehabilitation interventions will be carried out 5 days per week for a total of 12 weeks. All outcomes will be measured at baseline, 4 weeks, 8 weeks, and 12 weeks during the intervention and 1 month, 3 months and 6 months during the follow-up period. The effectiveness outcomes will be included visual analog scale, isokinetic knee muscle strength, Knee Injury and Osteoarthritis Outcome score and 36-Item Short-Form Health Survey score; The act mechanism outcomes will be included motor evoked potential, grey matter density, white matter, subcortical nuclei volumes, cortical thickness and functional connectivity by MRI. Two-way of variance with repeated measures will be used to test the group and time effect for outcome measures.

**Discussion:**

The study will be the first protocol to examine whether there are synergistic effects following high-frequency rTMS combined with quadriceps strength training for treat KOA and clarify the mechanism of action. High-frequency rTMS can be added into the training program for KOA patients if it is proven effective.

**Trial registration:**

Chinese Clinical Trial Registry ChiCTR2300067617. Registered on Jan.13,2023.

## Background

Knee osteoarthritis (KOA) is a chronic degenerative joint disease characterized by degenerative cartilage lesions and secondary bone hyperplasia of the knee joint [1]. KOA accounts for more than 80% of total osteoarthritis and is the leading cause of disability, decrease quality of life in the adult and elderly population [2]. The management of KOA may be requiring long-term treatment, leading to significant financial strain on individuals, families, and society as a whole. Consequently, it is imperative to investigate and find effective therapeutic approaches for individuals with KOA, benefiting both the affected individuals and society at large.

To date, there is no proven treatment method that can reverse the course of KOA [3]. Current therapeutic strategies for KOA are focus on improving muscle strength or relieving pain, including medication, physical exercise, intra-articular injection, etc. Clinical guidelines recommend physical exercise as one of the most critical non-pharmacological treatments of KOA [4], which has been proven to improve knee function effectively [5]. Quadriceps strengthening is an critical component of the exercise program because it has been found that patients with KOA always have significant quadriceps weakness [6]. Previous studies indicate quadriceps strengthening is benefit for the relief of knee joint pain and stiffness and improving quality of life [7–9]. Although exercise is effective in KOA, a recent meta-analysis indicated its treatment benefits are moderate for pain and function, performance at or nearest to 8 weeks. Besides, the exercise effects appeared to peak around 2 months and then gradually decreased and became no better than usual care after 9 months [10]. It means the effects of exercise will plateau and pain always persist. Leandro et al. [11] also have proved that exercise treatment effectiveness and adherence seem to decrease over time.

In recent years, more and more evidence has proved that low activation of M1 [12] and secondary to gamma loop [13] and motor-sensory circuit disorders [14] may be potential reasons for weakness of quadricep muscles in KOA. It can be seen that the enhancement of muscle strength for KOA is not only about the improvement and optimization of muscle strength training program, but also about the activation of brain areas. Therefore, the M1 may be a potential neurotherapeutic target for therapy in KOA [15]. Furthermore, another study showed that chronic pain in KOA can also further increase motor cortex inhibition. The chronic pain in KOA patients is not necessarily related to damage to the peripheral muscular system, but rather to neuroplastic changes in pain-related circuits that result in maladaptive neuroplasticity and lead to a perpetuation of pain [16]. The neuroplasticity changes in response to constant peripheral pain and less intracortical inhibition, which leads to enhance the levels of pain and dysfunction [17, 18].

Non-invasive brain stimulation is an increasingly growing domain of rehabilitation therapeutics for clinical neurological disorders. A variety of techniques for transcranial brain stimulation has been proposed, such as, Transcranial Direct Current Stimulation (tDCS), Transcranial Magnetic Stimulation (TMS) [19]. A general opinion is that modulation of neuronal excitability by tDCS is a relatively simple function (e.g., cortical excitability is reduced by cathodal stimulation and increased by anodal stimulation) and tDCS effects are difficult to predict, rarely used to treat diseases with various neural circuits, such as, pain related to central sensitization [20]. For rTMS, the magnetic field pulse delivered by a stimulating coil applied on the scalp is able to pass through skull bone without being attenuated and to generate an electric field when entering the brain. The intensity of the induced current is sufficient to produce action potentials and to activate brain networks safely and painlessly [21]. rTMS has been proposed to treat various pain syndromes related to central sensitization phenomenon, a Level A of definite analgesic effect was stated for the use of high frequency rTMS of M1 applied contralaterally to the pain side in patients with neuropathic pain. Previous study demonstrated that the chronic pain associated with KOA may develop in connection with a maladaptive process of pain sensitization in the central nervous system [22]. Hence, there is a basis for speculation that rTMS could be beneficial in alleviating pain associated with KOA.

Although the positive rehabilitation effect of quadriceps strengthening and high-frequency rTMS for KOA have been demonstrated, respectively, the synergistic effect of the combination of the two for treat KOA is still unclear. Therefore, the randomized controlled trial is designed to observe whether high-frequency rTMS combined with quadriceps strength training can better improve the knee function and reduce pain in KOA patients than quadriceps strength training alone and explore the mechanism of this combined rehabilitation. The study will provide a new perspective on the treatment of KOA.

## Methods

### Study design

This study will be a randomized controlled trial with a parallel-group design. A total of 148 eligible participants will be assigned to the quadriceps strength training (QT group); high frequency rTMS (HT group); sham rTMS and quadriceps strength training (ST + Q group); high frequency rTMS and quadriceps strength training (HT + Q group) at 1:1:1:1 ratio using stratified randomization with gender, age and Kellgren-Lawrence (KL) grade as factors. A brief flowchart of the entire study is shown in Fig. 1 and the schedule of events is provided in Table 1. The study protocol was approved by the Ethics Committee of Shanghai Seventh People’s Hospital (2022-7th-HIRB-065) and registered in the Chinese Clinical Trial Registry (ChiCTR2300067617).

**Fig. 1 Fig1:**
[figure not shown]
A brief flowchart of the entire study. TQPEAK, peak torque; TQPEAK/BW, TQPEAK adjusted for body weight; rTMS, repetitive transcranial magnetic stimulation; GM, grey matter density; WM, white matter; FC, functional connectivity; MRI, Magnetic resonance imaging

**Table 1 Tab1:**
[figure not shown]
Schedule of enrolment, intervention and assessments

"√" means things will be done

*VAS* Visual Analog Scale, *TQPEAK* peak torque, *TQPEAK/BW* TQPEAK adjusted for body weight; agon/antag, agonist–antagonist ratio, *KOOS* Knee Injury and Osteoarthritis Outcome Score, *SF-36* 36-Item Short Form Survey, *GM* grey matter density, *WM* white matter, *FC* subcortical nuclei volumes, cortical thickness; functional connectivity

### Sample size calculation

The sample size was determined based on the priori power analysis through G*Power software version 3.1.9.2. OMERACT-OARSI hip and knee osteoarthritis core outcome set [23] showed that the pain is the most core outcome and the percentage frequency is 94.8% from 1997 to 2017. Furthermore, Guinot et al. [24] reported that the effect size of rTMS for improve pain score in patients with fibromyalgia was 0.24. Therefore, the effect size was set as 0.24 in the present protocol. In the calculations, ANOVA repeated measures between factor was chosen, effect size 0.24, alpha 0.05, power 0.80, number of groups 4, number of measures 6, and the sample size was calculated as 116. Taking into account a conservative anticipation of a 20% drop-out rate, the final sample size will therefore be 37 in each group, with a total of 148 subjects.

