### Outcomes

Participants will be assessed by other physiotherapists blinded to the group allocation at different time points based on different assessments shown in Table 1. Additionally, baseline age, gender, symptoms, disease severity, duration, previous treatment and medication will be recorded using a questionnaire (in week 0). The primary end-point is the 12 weeks and all side effects during the study also will be recorded in real time.

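### The stated 80% power belongs to a four-arm effect averaged over six visits, not to the 12-week end-point or to HT+Q versus quadriceps training alone

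*Protocol article*

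**What the plan says.** The Sample size calculation section of the protocol article describes a G*Power calculation: "ANOVA repeated measures between factor was chosen, effect size 0.24, alpha 0.05, power 0.80, number of groups 4, number of measures 6". The effect size comes from a study of rTMS in fibromyalgia. The result is 116, raised for 20% drop-out to 37 per arm and 148 in total. The section does not state the correlation assumed among the repeated measures.

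The Outcomes section fixes the time point: "The primary end-point is the 12 weeks". VAS is named under the primary effectiveness outcomes. The Background gives the question as whether the combination "can better improve the knee function and reduce pain in KOA patients than quadriceps strength training alone"; the Abstract and the Discussion put it the same way.

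The Abstract and the Statistical analysis section plan a two-way repeated-measures ANOVA for group and time effects. Bonferroni correction is reserved for post hoc comparisons and used only if needed. The Abstract lists seven assessment times, baseline included.

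**The concern.** Three targets are in play. The power calculation concerns a test with 3 numerator degrees of freedom, comparing four arms on the mean of six visits. The primary end-point is a single visit. The scientific question is one contrast between two arms. The sample-size section gives a power only for the first and does not say that the figure is limited to it.

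Averaging over visits reduces the variance of each arm mean, and here it supplies much of the 80%. It also assumes that the effect size applies to the visit average. The Background itself reports that exercise effects peak at about two months and then decline, so a constant difference between arms through six months of follow-up cannot be taken for granted.

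The interpretation of the result is at stake. If HT+Q does not differ significantly from training alone at week 12, the trial could be cited as an 80%-powered negative result on synergy. The documents do not establish that power for that comparison.

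**Working it through.** **Inputs from the documents.** f = 0.24, alpha 0.05, k = 4 groups, m = 6 measures, N = 116 (29 per arm), 148 enrolled (37 per arm), 1:1:1:1 allocation. **Assumed:** correlation between visits rho = 0.5, with a range shown; 0.24 is Cohen's f, as this G*Power routine takes it.

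**1. Reproduce the plan's figure.** For the between-factors test, lambda = N f² m / (1 + (m − 1) rho), with df k − 1 and N − k.

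- N f² = 116 × 0.0576 = 6.68.
- At rho = 0.5 the averaging factor is 6 / 3.5 = 1.71, so lambda = 11.45 and power = 80.6%.
- The smallest balanced N reaching 80% is 116, which agrees with the plan.
- Drop-out: 116 / 0.8 = 145, rounded up to 37 per arm = 148. This also agrees.
- Using m = 7 instead of 6 still gives 116 in balanced arms.

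**2. Sensitivity to the unstated correlation** (same test, N = 116):

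| rho | Power | Balanced N for 80% |
|---|---|---|
| 0.3 | 92.6% | 84 |
| 0.5 | 80.6% | 116 |
| 0.6 | 74.6% | 132 |
| 0.7 | 68.9% | 148 |
| 0.8 | 63.8% | 164 |

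**3. Four-arm test at week 12 only.** Set m = 1, so lambda = N f².

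- N = 116: lambda = 6.68, power 55.1%.
- N = 148: lambda = 148 × 0.0576 = 8.52, power 67.2%, if carried-forward values do not dilute the effect.
- 80% would need 196 evaluable (49 per arm).

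**4. HT+Q against one training arm at week 12.** An f of 0.24 across four arms fixes a two-arm difference d (in SD units) only once the pattern of means is given. Power is from the two-sided noncentral t with 29 per arm, unadjusted for baseline.

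| Pattern of arm means | d | Power, alpha 0.05 | Power, alpha 0.05/6 |
|---|---|---|---|
| Two arms against two | 2f = 0.480 | 43.5% | 19% |
| Only HT+Q differs | 4f/√3 = 0.554 | 54.6% | 28% |
| QT and ST+Q equal, largest possible d | f√6 = 0.588 | 59.5% | 32% |
| Evenly spaced, the two arms at the ends | 3f/√1.25 = 0.644 | 67.4% | 40% |
| The two arms at the ends, the other two midway | f√8 = 0.679 | 71.9% | 45% |

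The first three rows are those in which QT and ST+Q have equal means (43% to 60%). The last row is the maximum over all patterns. The first row is not a strict minimum, because a pattern in which most of the spread lies in other arms gives a smaller d. The last column applies only if all six pairs are corrected by Bonferroni.

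**5. Detectable difference, 29 per arm, 80% power, two-sided 0.05.** (2.003 + 0.848) × √(2/29) = 0.75 SD. With baseline adjustment at an assumed correlation of 0.5: 0.75 × √(1 − 0.25) = 0.65 SD.

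**6. Against the 1.16 MCID for VAS.** The documents give no VAS SD. For illustration, unadjusted with 29 per arm: SD 1.5 gives d = 0.77 and 82% power; SD 2.0 gives d = 0.58 and 58%; SD 2.5 gives d = 0.46 and 41%.

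**The case against.** The strongest reply is that the calculation is correct and fits the plan. Both the 116 and the 148 reproduce, and the test used is the group effect of the repeated-measures ANOVA that the protocol intends to run. Sizing on the planned model is ordinary practice. All of this stands: there is no arithmetic error and no conflict with the planned ANOVA. What remains is that the protocol also fixes a 12-week primary end-point and a specific contrast, and the 80% describes neither.

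Second, last observation carried forward would keep up to 148 in the analysis. That raises the four-arm power at week 12 to 67% at best, still below 80%. With 37 per arm the unadjusted pairwise contrast passes 80% only for the most extreme pattern of means (82%).

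Third, baseline adjustment would help. At a correlation of 0.5 the four-arm test at week 12 reaches 69% with 116, and the pairwise contrast ranges from 55% (d = 0.48) to 83% (d = 0.679). The Statistical analysis section does not describe such adjustment, so the protocol cannot rely on it as written.

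Fourth, the Bonferroni column may not apply. The protocol makes the correction conditional, and a single pre-named contrast would not need it.

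**Conclusion.** The point holds as a mismatch between the test that was powered and the end-point and question that were declared. At f = 0.24, power at week 12 is about 55% for the four-arm test with 116 completers (67% with 148, undiluted). It is about 43% to 72% for the unadjusted pairwise contrast with 29 per arm, or 43% to 60% if QT and ST+Q have equal means. These figures rest on 0.24 being Cohen's f and applying in full at week 12, and on the patterns of means listed.

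A reader might infer that power for the trial's question is at most 55%. The documents do not support that: the figure depends on the pattern of means, on how many are analysed and on baseline adjustment, and several of these combinations exceed 55%. A reader might also infer that the sample-size arithmetic is wrong, or that 148 must be increased. Neither follows: the arithmetic reproduces, and the effect size is borrowed from another disease, so the 196 in the working shows scale only. Nor can a power be given for an effect that builds and then fades, because the documents give no time profile.

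**What to change.** Keep 148 and revise the Sample size calculation section:

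1. State the assumed correlation among visits (0.5 reproduces the figure) and show how power changes over a plausible range.
2. Say that the 80% applies to the four-arm group effect averaged over six visits.
3. Add the power or detectable difference for VAS at week 12 for HT+Q against quadriceps training alone. The sponsor should name the comparator: the wording points to QT, while ST+Q is the arm that controls for sham stimulation. With 29 per arm at two-sided 0.05, the detectable difference at 80% power is about 0.75 SD.
4. If the sponsor also adopts baseline adjustment, this becomes about 0.65 SD at an assumed baseline correlation of 0.5. That changes the analysis, so the Statistical analysis section would have to say so.
5. Compare with the 1.16 MCID only under a stated, assumed range of VAS SD.

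Items 1 to 3 and 5 cost a rewritten paragraph and no extra participants; item 4 also needs the analysis text amended. The downside is that the stated power becomes less favourable. The article describes the trial as still in preparation, so the change can be made before recruitment.

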### Recruitment, enrollment and randomization procedures

All patients with KOA will be recruited from the orthopedics or joint surgery department of Shanghai Seventh People’s Hospital in China and communities around the hospital. Recruitment methods will include posters, online advertisements, and leaflets. We will communicate with prospective participants about the study details. After the patients voluntarily sign the informed consent, they will be invited to participate in the study. Recruitment will start from 1 October 2023, until when 148 participants are enrolled.

A total of 148 eligible participants will be assigned to four groups at a 1:1:1:1 ratio using stratified randomization with gender, age and KL grade as factors in this research. The stratified randomization will be achieved as follows: Firstly, participants will be invaded into men and women two groups. Secondly, the two groups will be grouped by age (< 50 and ≥ 50). Lastly, the four groups will be grouped by KL grade (II and III), a total of 8 subgroups. In these eight subgroups, the subjects will be randomly regrouped the QT group, HT group, ST + Q group and HT + Q group. Finally, all four groups will be regrouped into four new groups to minimize the bias of the final results. The randomization procedure is performed by an independent research assistant who is not comes into contact with the participant at any point prior to randomization and is not involved in the data collection using Microsoft Excel to generate the random number (https://www.microsoft.com).

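### The sample size rests on six measures that all carry the effect; the planned ANOVA does not say how baseline enters, and as a time level it would cut power at 116 from about 80% to about 67% (correlation 0.5)

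*Protocol article*

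**What the plan says.** - **Sizing (Sample size calculation).** The G*Power routine is identified by "ANOVA repeated measures between factor was chosen", with "effect size 0.24, alpha 0.05, power 0.80, number of groups 4, number of measures 6, and the sample size was calculated as 116". A 20% drop-out allowance takes this to 37 per group, 148 in total. The section gives no correlation among the measures and does not say which visits make up the six.
- **Schedule (Abstract, Methods).** "All outcomes will be measured at baseline, 4 weeks, 8 weeks, and 12 weeks during the intervention and 1 month, 3 months and 6 months" of follow-up. That is seven assessments, six of them after baseline.
- **Analysis (Abstract, Methods, repeated in substance under Statistical analysis).** "Two-way of variance with repeated measures will be used to test the group and time effect for outcome measures". Neither section says whether baseline is a time level, a covariate, the reference for change scores, or left out. Statistical analysis also fills missing values by carrying the last observation forward.
- **End-point (Outcomes).** The primary end-point is set at 12 weeks.

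**The concern.** The between-factor routine tests the group difference in each participant's mean over the measures entered. It takes the stated effect to be present at all of them. Under randomisation the expected group difference at baseline is zero. Adding baseline to the averaged measures therefore dilutes the group difference and barely reduces the variance of the mean.

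Six measures fits the six post-baseline visits, but the analysis text does not restrict the test to them. Read as written, a two-way ANOVA for group and time on an outcome measured at seven scheduled visits has seven time levels, baseline among them. The sizing and the analysis would then describe different tests. At the correlation that reproduces 116, a true effect of the assumed size would be missed by about one in three such trials with 116 completers, against the intended one in five.

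**Working it through.** **Inputs from the Sample size calculation section:** f = 0.24, alpha 0.05, k = 4 equal groups, m = 6 measures, N = 116, enrolled total 148.

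**Assumptions, not in the document:** compound symmetry with correlation rho; rho = 0.5 as base case because it reproduces 116, with 0.3 and 0.7 as a range; f = 0.24 at every post-baseline visit; no expected group difference at baseline.

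**Formula.** lambda = N f² m / [1 + (m − 1) rho], with F on k − 1 = 3 and N − 4 degrees of freedom.

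**1. The plan's own figure.** m = 6, rho = 0.5, N = 116: lambda = 116 × 0.0576 × 6 / 3.5 = 11.45, power 80.6%. At N = 112 power is 79.0%, so 116 is the smallest balanced total reaching 80%. Drop-out: 116 / 0.8 = 145, rounded up to 4 × 37 = 148. Both printed totals reproduce.

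**2. Seven measures, all carrying the effect.** lambda = 116 × 0.0576 × 7 / 4 = 11.69, power 81.5%. The count of seven against six costs nothing.

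**3. Seven measures, baseline null.** The averaged effect is 6/7 of 0.24. The variance of the mean (in units of the single-visit variance) goes only from 3.5/6 = 0.583 to 4/7 = 0.571. So lambda = 11.69 × (6/7)² = 8.59 and power is 67.2%. A simulation of 20,000 trials with 29 per arm also gives 67.2%. The total needed for 80% is 152. With all 148 analysed, lambda = 10.96 and power is 79.0%.

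**4. Dependence on rho, N = 116:**

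| rho | Six post-baseline | Seven, baseline null | Loss (points) |
|---|---|---|---|
| 0.3 | 92.6% | 83.5% | 9.1 |
| 0.5 | 80.6% | 67.2% | 13.4 |
| 0.7 | 68.9% | 54.6% | 14.3 |

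**5. If the six were meant to include baseline**, only five carry the effect. The factor is 5/6, lambda = 11.45 × (5/6)² = 7.95, and power is 63.4%.

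**6. Six post-baseline visits with baseline as covariate.** The residual variance of the mean is (1 + 5 rho)/6 − rho². At rho = 0.5 this is 0.583 − 0.25 = 0.333, so lambda = 116 × 0.0576 / 0.333 = 20.05. On 3 and 111 degrees of freedom power is 97.1%. At rho = 0.3 it is 97.3% and at rho = 0.7 it is 99.3%.

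**The case against.** The strongest reply is that this argues from silence. An article may leave the handling of baseline to the full protocol or analysis plan, no sentence makes baseline a time level, and six is exactly the number of post-baseline visits. All of that stands. It rules out calling 116 an error, and it makes the 67% conditional.

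Further points, and what remains of each:

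- **Meaning of 0.24.** If 0.24 is already the effect averaged over whatever measures enter, there is no dilution. It is taken from a fibromyalgia study that is not at hand, so this cannot be settled. A per-visit effect is an assumption.
- **Seven visits.** The abstract applies the schedule to all outcomes, yet the MRI section has scans only at baseline and after 12 weeks, and the body of Table 1 is not shown. The count is therefore the abstract's. It is the only visit list available for the pain score.
- **All 148 are analysed.** With values carried forward, power is 79.0%, close to target. That holds only if carried-forward values do not shrink the effect. As an illustration, a 10% shrinkage gives lambda = 10.96 × 0.81 = 8.88 and about 69%.
- **Relevance.** The primary end-point is 12 weeks, and these figures describe only the omnibus group test. That is nevertheless the test on which the trial was sized.

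A reader might go further and infer that the trial simply has 67% power, or that six against seven is itself the mistake. The document supports neither. The first needs a time-level baseline, correlation 0.5 and 116 completers together; at correlation 0.3 power stays above 80%. Step 2 refutes the second.

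**Conclusion.** The concern holds in conditional form. The stated power is reached when the group effect is tested on the six post-baseline visits, and the analysis text does not say so. If baseline is a time level, the omnibus group test loses about 9 to 14 points of power at 116 over correlations 0.3 to 0.7. The loss itself does not depend on the undisclosed correlation being 0.5; whether power falls below 80% does. Everything rests on compound symmetry and a constant effect of f = 0.24 after baseline. This is an unspecified analysis choice with a simple and favourable resolution.

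**What to change.** In the abstract's Methods and in Statistical analysis, state that the group effect is tested on the six post-baseline visits, with baseline removed from the repeated factor and entered as a covariate. In Sample size calculation, say that the six measures are those visits and give the assumed correlation. The six measures and the total of 116 then stand, and power exceeds the stated 80% under the same assumptions.

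If baseline is kept as a time level, restate the measures as seven, with no effect expected at the first, and report the lower power: about 67% at 116 completers, or 79% if all 148 are analysed without dilution, both at correlation 0.5.

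The cost is two or three sentences. Baseline is already collected, so no patients or visits are added. Keeping the ANOVA unchanged costs only a less favourable power statement.
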